### Participant Timeline

Baseline scores will be collected for all groups. Follow-up scores will vary depending on group and will be collected at 6 and 12 weeks (all groups) and 16 and 28 weeks (intervention groups II and III) (see Figure 5 for flow chart).

### Sample Size

This study is mainly powered on the primary outcome, the detection of a significant difference between the three degrees of care (usual, additional website, additional counseling) on medication adherence as determined by refill records of computerized pharmacy systems. Based on previous research in our population and data from the literature [26], we estimate that the adherence at the start of the study will be 65% in each group with a standard deviation (SD) of 30%. We hypothesize that the intervention given in group II and the intervention given in group III will result in an increase of 10% in adherence to treatment, resulting in mean adherence rates of 75% and 85% in groups II and III, respectively. To detect these differences in medication adherence the estimated group size with a power of 80% and an alpha of .05 (2‐sided) would be 200 in each group, resulting in 600 participants in total.

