**Methods:**

In this study the effect of a personalized visualization of cardiovascular risk levels through a website aiming at supporting self management in combination with a group consultation and communication intervention by a nurse on adherence to treatment in 600 patients with manifest cardiovascular diseases will be assessed. The health belief model was chosen as main theoretical model for the intervention.

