### Trial Design and Aim of the Study

The study will use a single‐center, prospective, randomized controlled clinical trial design and examine the effectiveness of a new intervention that incorporates HBM and behavior change strategies to improve adherent behavior in cardiovascular patients. The intervention consists of a patient-based screening method, a specific nurse-based intervention (structural informative consulting and motivational counseling), and personalized visualization of cardiovascular risk levels via a website. The objective is to test the effectiveness of this intervention to improve medication adherence in patients with established CVD (ie, in secondary prevention).

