### Intervention

For the intervention, participants will be split in three groups. Participants in group I (control group) receive only usual care. Group II participants receive usual care plus access to a personalized website. For the group III participants, in addition to usual care and access to the personalized website, the intervention program will also include a single group consultation of 60 minutes led by a nurse and a pharmacist followed by two individual consultations of 30 minutes with a nurse.

We want to test if treatment II (only the Web portal) can give the same results as treatment III (the Web portal and the single group consultation followed by two individual consultations). The need for low-cost effective interventions in our health care system led to the motivation for this 3-arm protocol.

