## Results

### Primary Outcome

The primary outcome of our study is adherence to the CVD medication (classified by the Anatomic Therapeutic Chemical classification system) measured with a dedicated calculation of refill data of the used plated aggregation inhibitors and lipid modifying agents obtained from patient’s pharmacy.

Refill records of computerized pharmacy systems will be collected from 3 years prior to a patient’s cardiovascular event through up to 3 years after the study follow‐up period. Prescription records include the names of all of the dispensed drugs, prescribed daily dose, quantity dispensed at each pharmacy fill, and the dates of the prescription fills. Adherence will be calculated for the CVD medications as the theoretical duration divided by the period between the start date and the date of the last prescription filled. The theoretical duration will be calculated by dividing the number of units dispensed by the prescribed daily dose [25].

Patients with an adherence level of at least 80% will be classified as adherent, and patients with an adherence level less than 80% will be classified as nonadherent. Secondary prevention studies showed that patients with an adherence of less than 80% have an increased risk of death [26].

Refill adherence rates have been used extensively for the assessment of drug acquisition and dispensing. Compared with electronic monitoring, refill data provide researchers with a relatively simple method for investigating exposure to medication in large populations [27-29]. Moreover, this method is suitable for investigating long‐term persistence to treatment and gaps in medication supply [30].

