### Statistical Methods

The data will be analyzed based on the intention‐to‐treat principle and evaluated using SPSS, with descriptive statistics (mean, median, SD, and interquartile range) being determined for all variables. The data will be presented in quantitative format (eg, biometrics, laboratory results, blood pressure, lifestyle scores, adherence score on the basis of refill data, and the MMS) and in descriptions of observed effects (eg, change in BMQ, determinants for adherence, evaluation of the use of iVAZ, and appreciation of nurse intervention).

To evaluate the difference between the groups, an analysis of variance test will be performed on the outcome measures for the three patient groups. The independent variable will be the three intervention groups. The dependent variable is medication adherence measured with the dedicated calculation of refill data. Specifically, we will compare the difference between the first and last time-point between groups for the primary and secondary outcomes measures. For the intervention groups II and III, we will also compare the outcomes of the clinical data at 16 and 28 weeks. To correct for multiple comparison, a Duncan’s multiple range test will be performed. Furthermore, we will perform a receiver operating characteristic (ROC) curve analysis to compare the outcome of the screening instruments (MMS and BMQ) with the pharmacy refill dates. In the ROC curve plot, specificity of the questionnaire is on the x-axis and sensitivity of the question is on the y-axis.

Plausible relations between parameters of cardiovascular risk factors, motivation to change, socioeconomic class, and parameters of adherence (calculated refill score and BMQ and MMS scores) will be tested in a univariate manner. Individual parameters will be tested for normality using the Kolomogorov-Smirnov test in order to select adequate univariate tests. Multiple logistic regression analysis will be performed to assess the relative importance of selected parameters for the likelihood of low adherence, as defined by the refill data algorithm. In all analyses, potential confounders will be included if they independently changed the beta coefficient for dedicated calculation of refill data by at least 5% or when consensus about inclusion existed within the team of researchers supported by clinical evidence from literature.

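### The stated objective (III versus I), the reason for three arms (II the same as III) and the planned test (undirected ANOVA with Duncan's test) ask different questions, and no contrast is tied to the objective

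*Protocol article*

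**What the plan says.** Four places in the protocol article bear on what the trial is meant to decide.

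- **Objective.** Trial Design and Aim of the Study: "The objective is to test the effectiveness of this intervention to improve medication adherence in patients with established CVD". The intervention is in the singular and is defined as a package: "The intervention consists of a patient-based screening method, a specific nurse-based intervention", plus the website. The Methods paragraph of the Abstract agrees, describing the website "in combination with a group consultation and communication intervention by a nurse on adherence to treatment in 600 patients". Only group III gets website and nurse consultations together, so this points to III versus I.
- **Reason for three arms.** Intervention: "We want to test if treatment II (only the Web portal) can give the same results as treatment III". This is II versus III, and a question of sameness.
- **Powering.** Sample Size: the trial is sized for "the detection of a significant difference between the three degrees of care (usual, additional website, additional counseling) on medication adherence", with expected means of 65%, 75% and 85%, SD 30%, 80% power, two-sided .05 and 200 per group. III is assumed 10 points better than II.
- **Analysis.** Statistical Methods: "an analysis of variance test will be performed on the outcome measures for the three patient groups", with Duncan's multiple range test for the pairs. The comparison is of the change from first to last time-point in refill adherence. No pair has priority, no testing order is given, and no margin is stated for II versus III.

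**The concern.** These are different hypotheses. An effectiveness objective for the package is answered by III versus I. A sameness question about the website is answered by II versus III against a margin. An omnibus ANOVA answers neither, because it asks only whether the three means are not all equal. Duncan's test then treats the three pairs alike and, being a test of difference, cannot show that two arms give the same result.

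The conclusion is therefore left open where it matters. A significant F does not say whether the website, the consultations or both did the work. A non-significant II versus III could be reported as the website matching the full programme, although it may reflect imprecision alone. Those two readings would lead to different decisions about whether to pay for nurse and pharmacist time.

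**Working it through.** **Inputs.** From Sample Size: n = 200 per group, control mean 65, SD 30, two-sided α = .05, expected means 65/75/85. Assumption: SD 30 is given for the adherence level, while Statistical Methods compares change, whose SD is not stated. SD 30 is used throughout. Means other than 65/75/85 are illustrations.

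**1. Does the sample size reveal the deciding contrast?** For two means, n = 2(1.96 + 0.842)² × SD²/δ².

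- III versus I, δ = 20: 2 × 7.85 × 900/400 = 35.3, so 36 per group.
- II versus I or III versus II, δ = 10: 2 × 7.85 × 900/100 = 141.3, so 142 per group.
- All three pairs with Bonferroni, δ = 10: 189 per group.
- Omnibus F at 65/75/85: 45 per group.

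None equals 200. A dropout allowance could bridge the gap (142/(1 − 0.29) = 200), but none is stated. The size does not identify a contrast.

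**2. What the omnibus F can tell apart.** Noncentrality λ = n × Σ(mean − grand mean)²/SD², with 2 and 597 df.

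| True means I/II/III | Sum of squares | λ | Power of F |
|---|---|---|---|
| 65/65/75 (website adds nothing) | 11.11 + 11.11 + 44.44 = 66.67 | 200 × 66.67/900 = 14.8 | 94% |
| 65/75/75 (website does everything) | 44.44 + 11.11 + 11.11 = 66.67 | 14.8 | 94% |
| 65/70/75 | 25 + 0 + 25 = 50 | 11.1 | 85% |
| 65/75/85 (protocol) | 100 + 0 + 100 = 200 | 44.4 | over 99.9% |

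The first two rows are identical to the F test, yet they are the two answers that the three-arm design was built to distinguish.

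**3. How often II versus III could be misread.** The standard error of a difference is 30 × √(2/200) = 3.0 points. Power is 91% for a true 10-point pair and 38% for a true 5-point pair. At true means 65/70/75, simulation gives III versus I significant and III versus II not in about 54% of trials with each pair at .05, and about 52% with Duncan's test. If the observed means were exactly 65/70/75, F = 200 × 25/900 = 5.56 (p about .004) and III minus I = 10, which is significant. But III minus II = 5, with 95% CI 5 ± 1.96 × 3, or −0.9 to 10.9. That interval still contains the 10-point advantage assumed in Sample Size, so it is no evidence of sameness.

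**4. The protocol's own scenario.** At 65/75/85, each 10-point pair has about 91% power, III versus I over 99.9%, and all three pairs are significant in about 83% of simulated trials.

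**5. Family-wise error.** Duncan's range test on three means rejects under the global null with probability 1 − 0.95² = 9.75% if not preceded by a significant F (simulation: 9.7% to 9.8%). After a significant F it is 5.0%. The article does not say that the F gates it. Testing III versus I at .05, then II versus I at .05 only on success, holds 5%: if III equals I, an error requires the first test to reject. If III differs from I, only the second test can err.

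**The case against.** The plan is not vague in every respect. Sample Size states a graded hypothesis and declares interest in both active arms. Statistical Methods names the outcome, the time-points, the test and a pairwise procedure. ANOVA with adjusted pairwise comparisons is a recognised approach to a three-arm trial, and under the stated means it would usually separate all three arms. Testing order is also often left to an analysis plan or full protocol, neither of which is shown. All of this is fair and limits the size of the point. What stands is that the article's own sections contradict each other: II as good as III in one place, III 10 points better in another (the Discussion likewise expects the combination to do better than either part), and an analysis that can establish neither the objective nor sameness. That is more than omitted detail.

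A reader might infer more than the document supports:

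- That the 80% cut ("Patients with an adherence level of at least 80% will be classified as adherent") is a rival primary endpoint. Sample Size and Statistical Methods size and test the mean, and no arm comparison on that class is planned.
- That three unadjusted pairwise tests will be run and the best one chosen. A multiple-comparison procedure is planned, so an error rate for unadjusted pairs does not describe this trial.
- That a positive F might arise because the website harms adherence. Nothing in the article suggests such a pattern.
- That the omnibus test is always the weaker one. At 65/70/75, III versus I has 91% power against 85% for F. At 65/65/75 and 65/75/75 the order reverses, 91% against 94%.

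**Conclusion.** The point holds as an inconsistency between objective, design rationale, powering and analysis, with no contrast tied to the objective. The F test has the same 94% power for opposite conclusions about the website, and at 65/70/75 about 54% of trials would yield a III versus II result open to being misread as sameness. It matters when effects are smaller than expected or not additive. Under the protocol's own 65/75/85 it is small. The figures assume 200 analysed per arm and SD 30 for the analysed quantity. A smaller SD of change would raise every power, but it would not help the F test tell the two website patterns apart. A reader might conclude that the trial could not be interpreted or that false positives are uncontrolled. The documents do not support that, since pairwise results will be available and error is 5.0% under the global null if Duncan's test follows a significant F.

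**What to change.** In Sample Size and Statistical Methods:

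1. Name group III versus group I on mean refill adherence as the primary contrast.
2. Test II versus I at two-sided .05 only if III versus I is significant.
3. Answer the question in the Intervention section by reporting III minus II with a 95% confidence interval, stating that non-significance does not show sameness unless a margin is set in advance. For orientation, 200 per arm with SD 30 and no true difference gives 80% power for non-inferiority (one-sided .025) at margins of about (1.96 + 0.842) × 3 = 8.4 points or more.
4. Make the omnibus ANOVA descriptive. Duncan's test is then not needed for the primary inference.

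The order is inferred from the Abstract and the stated aim. If the investigators hold II versus III to be the real question, they should say so and set a margin before seeing data.

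Cost: a few sentences, with no extra patients or data. II versus I cannot be claimed if III versus I fails, and the primary contrast has slightly less power than F in some patterns (91% against 94% at 65/65/75).

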### Recruitment

All cardiovascular patients who receive the regular cardiovascular preventive care will be asked to participate by a nurse when they arrive at the outpatient clinic for their screening consult. Patients will receive a letter explaining the study, documenting their ability to withdraw at any time without explanation, and confirming that their medical care will in no way be influenced by their decision regarding participation. At a minimum of 24 hours later, written consent will be sought by a research assistant prior to the patient entering the study.

We chose to include all cardiovascular patients in our study rather than only nonadhering patients as done in many other studies [6,9,34]. The reason is that we plan to do a 3-year follow-up and want to be able to see how adherence develops over time for initial adherers and nonadherers alike.

### Assignment of Interventions

Patients who meet the criteria and consent to participate will then be randomized by the nurse stratified by department (eg, neurology, vascular surgery, and cardiology) in a 1:1:1 ratio into one of the three groups using computer randomization.

### Blinding

The principal investigator and the researcher will be blind to randomization. However, due to the need for active participation, the patient, nurse, and pharmacist delivering the individual consultations will not be blind to assignment of individuals in group III.

### Data Collection and Management

The primary data collected will be provided by the initial screening. Obtained data from the screening are blood lipid levels, blood pressure, waist circumference, body mass index, blood glucose levels, and medication use. Lifestyle is evaluated through a questionnaire which is a compilation of existing validated questionnaires regarding demographic data, smoking, alcohol use, physical activity, and eating habits. For each of these lifestyle issues, patient’s motivation to change is evaluated [16]. Adherence is measured by the MMS [17] and beliefs about medication by the BMQ [18].

**Figure 5 figure5:**
[figure not shown]
Patient flow chart.

To monitor whether the website intervention is used, log‐in information per patient, expressed as the number of log‐ins and times and dates of log-in, will be recorded.

To measure the nurses’ performance skills required in the individual consultations, the behavior change counseling index will be used [35]. This validated checklist aims to measure the nurses’ competence in behavior change counseling and adaptation of motivational interviewing in healthcare settings. The group consultations are videorecorded and evaluated in order to validate the quality of the motivational interviewing techniques applied.

Data will be entered by the nurses who perform the screening and the intervention consults in iVAZ. iVAZ is a secured website which can only be entered by the participants by using their social security codes and by selected nurses using security codes. In addition, all patient pharmacists will receive a letter of information about the trial, consent of the ethical committee, and the informed consents of the participants. They will be asked to send the data on refill records of their computerized pharmacy systems through a secured email address. All the data will be anonymized according to the privacy protocols from the ethical committee and imported by the researcher into SPSS (IBM Corp).

### Statistical Methods

The data will be analyzed based on the intention‐to‐treat principle and evaluated using SPSS, with descriptive statistics (mean, median, SD, and interquartile range) being determined for all variables. The data will be presented in quantitative format (eg, biometrics, laboratory results, blood pressure, lifestyle scores, adherence score on the basis of refill data, and the MMS) and in descriptions of observed effects (eg, change in BMQ, determinants for adherence, evaluation of the use of iVAZ, and appreciation of nurse intervention).

To evaluate the difference between the groups, an analysis of variance test will be performed on the outcome measures for the three patient groups. The independent variable will be the three intervention groups. The dependent variable is medication adherence measured with the dedicated calculation of refill data. Specifically, we will compare the difference between the first and last time-point between groups for the primary and secondary outcomes measures. For the intervention groups II and III, we will also compare the outcomes of the clinical data at 16 and 28 weeks. To correct for multiple comparison, a Duncan’s multiple range test will be performed. Furthermore, we will perform a receiver operating characteristic (ROC) curve analysis to compare the outcome of the screening instruments (MMS and BMQ) with the pharmacy refill dates. In the ROC curve plot, specificity of the questionnaire is on the x-axis and sensitivity of the question is on the y-axis.

Plausible relations between parameters of cardiovascular risk factors, motivation to change, socioeconomic class, and parameters of adherence (calculated refill score and BMQ and MMS scores) will be tested in a univariate manner. Individual parameters will be tested for normality using the Kolomogorov-Smirnov test in order to select adequate univariate tests. Multiple logistic regression analysis will be performed to assess the relative importance of selected parameters for the likelihood of low adherence, as defined by the refill data algorithm. In all analyses, potential confounders will be included if they independently changed the beta coefficient for dedicated calculation of refill data by at least 5% or when consensus about inclusion existed within the team of researchers supported by clinical evidence from literature.

Missing data is unfortunately very common in eHealth research. We follow the recommendation for eHealth research to use the multiple imputation technique in SPSS when analyzing our dataset with missing observations [36].

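### Pairwise arm comparisons share one variance pooled over three arms; if spread differs by arm at follow-up, a two-arm contrast gets a slightly wrong standard error

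*Protocol article*

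**What the plan says.** Under Statistical Methods, the Protocol article states that "an analysis of variance test will be performed on the outcome measures for the three patient groups". The pairwise step is also fixed: "To correct for multiple comparison, a Duncan’s multiple range test will be performed". The variable compared is a change: "we will compare the difference between the first and last time-point between groups for the primary and secondary outcomes measures". No unequal-variance version of either procedure is named.

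Under Sample Size, the only spread given belongs to the start of the study: "65% in each group with a standard deviation (SD) of 30"%. The interventions are expected to move the arms apart, "resulting in mean adherence rates of 75% and 85% in groups II and III, respectively". The article gives no follow-up SD by arm, no SD of change and no correlation between baseline and follow-up. Allocation is 1:1:1 with 200 per group. The Primary Outcome section defines adherence as a refill ratio and states no cap at 100%.

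**The concern.** Ordinary ANOVA and Duncan's test estimate one error variance, the average of the three arm variances when the arms are equal in size, and apply it to every pair. That is right only if the arms share a common spread. The one SD in the plan describes a moment when all three arms sit at 65%. If group III moves to 85%, many of its patients may collect near full adherence and its spread may fall.

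Equal arms largely protect the overall F test against unequal variances. They do not protect a single pair: group I versus II would borrow precision from a tighter group III, and group II versus III would take on noise from a wider group I.

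These two contrasts carry the low-cost question that motivates the three arms (Intervention section). If only the consultations work, the portal-versus-control test would be somewhat too liberal. If the portal does as well as the consultations, the test between them would be somewhat too conservative.

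**Working it through.** **The plan's own figure.** The document gives no error rate for pairwise tests. Its group size of 200 is not reproduced by the plain two-mean formula: 2 × (1.960 + 0.842)² × 30² / 10² = 141.3, so 142 per group. At 200 per group the power for 10 points is 91.5%. The point below does not depend on this difference.

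**Inputs from the document.** Baseline mean 65% and SD 30; planned means 75% and 85%; 200 per arm; two-sided alpha 0.05; comparison on the first-to-last difference.

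**Assumptions, not in the document.**
- Group I stays at 65%.
- Adherence is capped at 100%, with a beta-type spread proportional to √(m(1 − m)) and anchored at 30 for m = 0.65. At m = 0.85 the SD is 30 × √(0.1275/0.2275) = 22.5 (variance 504).
- The baseline to follow-up correlation r is the same in every arm and is varied.

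**Formula.** With equal arms the pooled variance is MSE = (V_I + V_II + V_III)/3, while the pair's own variance is the mean of its two arms. The ratio of the standard error used to the true one is R = √(MSE / pair variance), and the actual error of a nominal 5% test is 2 × (1 − Φ(1.96 × R)).

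**Change scores, as planned.** An arm that stays at 65% has V = 1800 × (1 − r). An arm that reaches 85% has V = 900 + 504.4 − 2r × 30 × 22.46.

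For r = 0.5 these are 900 and 730.6.
- Only the consultations work (I = II = 65, III = 85): MSE = (900 + 900 + 730.6)/3 = 843.5; R = √(843.5/900) = 0.968; I-versus-II error 5.8%. The standard error used is 2.90 points against a true 3.00.
- The portal does as well (I = 65, II = III = 85): MSE = (900 + 2 × 730.6)/3 = 787.1; R = √(787.1/730.6) = 1.038; II-versus-III error 4.2%.

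| r | V at 65% | V at 85% | I vs II error | II vs III error |
|---|---|---|---|---|
| 0 | 1800 | 1404 | 5.9% | 4.0% |
| 0.3 | 1260 | 1000 | 5.9% | 4.1% |
| 0.5 | 900 | 731 | 5.8% | 4.2% |
| 0.7 | 540 | 461 | 5.6% | 4.4% |
| 0.9 | 180 | 192 | 4.8% | 5.2% |
| 0.95 | 90 | 124 | 3.7% | 6.2% |

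**Reversal.** Setting 1800 − 1800r = 1404.4 − 1347.5r gives r = 395.6/452.5 = 0.874. Above this the arm that moved has the larger change variance, and both errors go the other way.

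**End values, for comparison only.** I versus II: R = √(768.1/900) = 0.924, error 7.0%. Duncan's test simulated at 200 per arm gave 7.0%, and 5.0% with equal SDs. II versus III: R = √(636.3/504.4) = 1.123, error 2.8%.

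**Sensitivity to the assumed SD (end values, I versus II).** A group III SD of 30 gives 5.0%; 27.5 gives 5.7%; 25 gives 6.3%; 20 gives 7.7%.

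**Own-variance tests.** In simulation on end values these gave 5.0% for I versus II and 4.8% for II versus III, where the pooled tests gave 7.1% and 2.7%.

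**The case against.** The strongest reply is that nothing in the document shows the spread to differ. A reader might infer that the planned means themselves force it to shrink. They do not: on a 0-100 scale the largest possible SD at a mean of 85 is 100 × √(0.85 × 0.15) = 35.7, so 30 remains possible. It would take an extreme shape (a beta distribution with mean 0.85 and SD 0.30 puts 69% of patients within 1 point of 0 or 100%), but even that argument needs a cap that the Primary Outcome section does not state.

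A reader might also infer that the portal-versus-control error is above 5% as planned. That is not supported either. At the planned means groups I and II differ, so no false positive between them can arise; the inflation needs I = II with III different. With all means and SDs equal there is none. The 7.0% belongs to end values, whereas the article compares changes, for which the excess is under 1 point and changes sign at high correlation.

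Nor can one say that a II-versus-III confidence interval is too wide, because the article plans no such interval.

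Finally, ANOVA with equal arms of 200 is a standard choice, and a robust variant could be settled in an analysis plan that is not shown. This limits the weight of the point but does not remove it: the article names specific methods that rest on a common variance, and the mechanism is correct.

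**Conclusion.** The point holds as a modest, conditional improvement and not as a demonstrated error. ANOVA with Duncan's test makes each two-arm comparison depend on the third arm's spread, and the document gives no follow-up spread by arm to show that this is harmless.

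Under the assumed shrinkage from 30.0 to 22.5 and correlations of 0.3 to 0.7, the planned change-score tests would run at about 5.6-5.9% for I versus II (only the consultations work) and 4.1-4.4% for II versus III (the portal does as well). Equal spreads give 5.0% for both. Size and direction rest on the assumed cap, the assumed beta-type spread and an unknown correlation. The figures are error rates per comparison; how well Duncan's test controls error over all three comparisons is a separate question.

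**What to change.** State that each pairwise comparison uses its own variance: Welch ANOVA for the overall test with unequal-variance pairwise tests, or a regression with heteroscedasticity-robust standard errors. This holds the error per comparison near 5% whatever the spread or the correlation, including where the direction reverses. Because Duncan's test is built on the pooled variance, the sentence should also name the multiplicity method that goes with the new pairwise tests.

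The cost is one sentence in Statistical Methods. With 200 per arm the degrees of freedom for a pair fall from 597 to at most 398, which moves the critical value from 1.964 to about 1.966. Sample size, data collection and conduct do not change.
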